#### Quality Control and Preventing Missing Data

Data collection is standardized by the use of a detailed manual of operations. The REDCap data entry system also has built-in logic to check data at the time of entry and minimize errors. Monthly data quality reports ensure that data are validated and data entry is completed in a timely fashion. If participants drop out, we are documenting specific reasons for drop out.

#### Planned Analysis

We will use a Cochran-Mantel-Haenszel test stratified by the randomization groups to test whether the odds of HTN control at 6 months differs between the intervention and control study arms. Statistical significance level will be set at the *P*<.05 level. We also will perform the same analysis at 12 months to examine if the difference between the intervention and control groups is sustained. Secondary analyses using the repeated BP assessments obtained at 6-month and 12-month visits are planned. We will use longitudinal generalized estimating equation models, with BP control modeled as a binary variable and average BP modeled continuously in separate models, with relevant covariates. Interactions will be tested to evaluate potential differential effects by baseline demographic and clinical characteristics.

We have planned for missing data. We are recording reasons for study drop out and will examine patterns of missingness. For the primary analysis, we will (multiply) impute the binary HTN control outcome. We are collecting a rich amount of covariate information on participants to inform the multiple imputation models.

We plan the following analyses to examine secondary outcomes related to system usability for care providers. The Welch *t* test will be used to examine the number of antihypertensive medication changes (dose adjustment, addition of new medications) per patient during the 6-month intervention period for the mGlide intervention arm. We will examine the provider mGlide experience using the Computer System Usability Questionnaire overall score as well as scores along the 3 principal factors identified on the Computer System Usability Questionnaire: System Usefulness, Information Quality, and Interface Quality. We also will collect qualitative feedback from providers using focus groups. These data will be analyzed using a qualitative framework including classic content analysis and microinterlocutor analysis [23,24].

Patient-reported outcomes (Table 2) will be examined by comparing whether there are group differences on the Patient Activation Measure [25], patient medication self-efficacy measure (Medication and Self-Efficacy Scale - Revised) [26], medication adherence (Hill-Bone Medication Adherence Scale) [27,28], self-reported health status (EQ-5D-3L) [29,30], and patient satisfaction with health systems and providers (Consumer Assessment of Healthcare Providers and Systems adult survey) [31] using a 2-sample *t* test separately at 6 months and 12 months after baseline. Finally, we will compare the rates of adverse events between the 2 trial arms using both adjusted and unadjusted negative binomial regression models with intervention as the key independent variable.

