### Visit Schedule and Assessments

Each participant completes a total of 3 visits: baseline visit and 2 follow-up visits at 6 months and 12 months postrandomization. The baseline visit includes informed consent in the participant’s language, randomization into one of the 2 study arms, participant education about HTN and BP control, baseline BP measurement using a protocol [18,19], and baseline surveys. The 2 follow-up visits include assessments of the primary and secondary study outcomes. In addition, team members call participants monthly (months 1-5) and bimonthly (months 8 and 10) to identify adverse events and address any challenges. Data collection details are presented in Table 2.

**Table 2 table2:** mGlide randomized controlled trial visit schedule and assessments at baseline and follow-up.

Measures		Baseline	6-month follow-up	12-month follow-up
Demographic information		x	N/A^a^	N/A
Medical history		x	N/A	N/A
Health behaviors (smoking, physical activity, diet, sleep)		x	N/A	N/A
Health insurance		x	N/A	N/A
Blood pressure		x	x	x

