**Patient-reported outcomes**				
	Health care experiences (CAHPS^b^ adult survey)	x	x	x
	Hill-Bone Medication Adherence Scale (HB-MAS)	x	x	x
	Medication and Self-Efficacy Scale - Revised (MASES-R)	x	x	x
	Patient Activation Measure (PAM-10)	x	x	x
	Health care utilization	x	x	x
	Self-reported health status (EQ-5D-3L)	x	x	x
	Technology usability (Marshfield System Usability Survey)	N/A	x	N/A

^a^N/A: Not applicable.

^b^CAHPS: Consumer Assessment of Healthcare Providers and Systems.

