### Randomization

Eligible and consented participants are randomized 1:1 to either an intervention mGlide arm or a state-of-clinical-care comparison arm. The randomization uses a site-specific randomization schedule and is stratified across the 4 participant groups discussed in Table 1. Randomization schedules follow from permuted blocks with randomly varying sizes to ensure approximate balance between the 2 study arms in each stratum across the trial while reducing predictability of the assignments.

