### Analysis

#### Outcomes

The main outcome will be the rate of HTN control at 6 months; the primary outcome will be defined as a binary indicator of uncontrolled HTN or death versus controlled HTN at 6 months. The BP is measured in-person in the clinical research center by a trained staff member who is blind to the patient’s assignment. The BP is measured 4 times using a standard digital monitor using proper technique, and the average of the last 3 BP measurements denotes the BP outcome. HTN control is defined as systolic blood pressure (SBP) <140 mm Hg, which is consistent with American College of Physicians, American Association of Family Physicians, and AHA primary and secondary stroke prevention guidelines [12,13,20]. The 2017 American College of Cardiology/AHA guidelines recommend a SBP goal of <130 mm Hg. The HTN treatment goals and target BP were discussed with the PCPs and clinical pharmacists at all sites prior to study recruitment. Everyone agreed to target a SBP goal of <140 mm Hg for intervention arm participants and requested that lower SBP goals be left to the discretion of the study pharmacists managing the patient. Study pharmacists have access to patient medical records. At 12 months, the BP outcome is assessed in the same manner as at 6 months. This allows the assessment of the secondary outcome of uncontrolled HTN or death versus controlled HTN at 12 months. Additional secondary outcomes include patient-reported medication adherence, medication use self-efficacy, self-reported health status, and quality of life that we assess with validated questionnaires at each of the 3 study visits. We ascertain participant adverse events and health care utilization during monthly phone calls during the first 6 months of the study and bimonthly in months 7-11. We also assess care providers’ experience of the mGlide system usability.

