#### Power and Sample Size

Sample size was calculated to address outcomes of failure to achieve HTN control or death at 6 months and 12 months after randomization. We based sample size calculations on (1) reported 1-year stroke survivor mortality rate of 4% [21] and assuming similar mortality among primary care participants with elevated CVD risk, (2) pilot results that showed a primary outcome rate of HTN control or death at 6 months of 15% in the intervention and 50% in the comparison groups [17], and (3) a 20% attrition rate. We identified that a sample size of 450 would provide at least 85% power, with an alpha of .05 to detect a 15% effect size. We planned for a more modest intervention effect size than achieved in our pilot results due to the longer period of observation and more diverse health systems and patient populations when compared to the pilot study. Similarly, while the loss to follow-up in the pilot study was very modest at 4%, we planned for a 20% attrition rate due to the economically stressed primary care population in our low-resource health systems. Nationally reported rates of uncontrolled HTN in stroke survivors are ~50% [7]. FQHC primary care rates of uncontrolled HTN are ~38%-40% [22]. Our sample size will allow valid subgroup analysis among the subgroup of primary care patients in all low-income sites (n=200) and the stroke survivor subgroup (n=100).

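### Patient-reported scores are compared with unadjusted t tests at each visit although every score is also measured at baseline, which costs precision on secondary outcomes

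*Protocol article*

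**What the plan says.** The relevant statements are all in the protocol article.

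- **Method (Planned Analysis).** "Patient-reported outcomes (Table 2) will be examined by comparing whether there are group differences on the Patient Activation Measure", followed by the medication self-efficacy scale (MASES-R), the Hill-Bone adherence scale, EQ-5D-3L and the CAHPS adult survey. The method is a two-sample t "test separately at 6 months and 12 months after baseline". No baseline score, stratum or other covariate is named.
- **Baseline data (Outcomes; Table 2).** The Outcomes section lists patient-reported secondary outcomes "that we assess with validated questionnaires at each of the 3 study visits". Table 2 marks all five tested instruments at baseline, 6 months and 12 months. The only survey without a baseline is technology usability, which is not among the five.
- **Design (Randomization).** Participants are "randomized 1:1 to either an intervention mGlide arm" or the comparison arm, and the schedule "is stratified across the 4 participant groups discussed in Table 1".
- **Other outcomes (Planned Analysis).** The primary test is stratified by the randomization groups. The repeated blood pressure data get longitudinal models with covariates. Adverse event rates get both adjusted and unadjusted models.

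**The concern.** A baseline score usually predicts the same person's later score. A t test on the follow-up score leaves that predictable variation in the error term, so the standard error is larger than it needs to be. The strata run from stroke survivors to low-income primary care patients, and variation between them also stays in the error.

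The article names this method outright, so it is a stated choice and not a detail left to a fuller document. It also differs from the way the article treats blood pressure, which is measured on the same visit schedule.

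At stake are wider confidence intervals and a lower chance of detecting real differences in adherence, self-efficacy and quality of life. These belong to the declared secondary aims. The primary outcome is not affected.

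**Working it through.** **No figure to reproduce.** The Power and Sample Size section says that "a sample size of 450 would provide at least 85% power", but this concerns hypertension control or death. It gives no standard deviation, detectable difference, power or correlation for any patient-reported score.

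**Inputs from the article.** There are 450 participants allocated 1:1, with 20% planned attrition: 450 × 0.80 = 360 evaluable, or 180 per arm. The 20% is a planning allowance, not observed loss of questionnaires.

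**Assumptions.** The baseline-to-follow-up correlation r is taken as 0.3, 0.5 and 0.7. Alpha is two-sided 0.05. The illustrative true difference is 0.25 SD.

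**Step 1: variance after baseline adjustment.** Relative to the follow-up-only t test, the variance of the adjusted arm difference is 1 − r² and the standard error is √(1 − r²). The equivalent t-test sample is 360 / (1 − r²).

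**Step 2: detectable difference at 80% power.** In SD units this is (1.960 + 0.842) × √(2/180) × √(1 − r²) = 0.295 × √(1 − r²).

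| | Variance factor | SE factor | Detectable difference (SD) | Power at 0.25 SD | Equivalent t-test sample |
|---|---|---|---|---|---|
| t test | 1 | 1 | 0.295 | 66% | 360 |
| Adjusted, r = 0.3 | 0.91 | 0.95 | 0.282 | 70% | 396 |
| Adjusted, r = 0.5 | 0.75 | 0.87 | 0.256 | 78% | 480 |
| Adjusted, r = 0.7 | 0.51 | 0.71 | 0.211 | 91% | 706 |

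**Step 3: would a change score remove the loss?** The article does not say that change scores are tested. If they were, with equal SDs at both times, the variance factor would be 2(1 − r): 1.40, 1.00 and 0.60 at r = 0.3, 0.5 and 0.7. The excess over the adjusted analysis is 2(1 − r) − (1 − r²) = (1 − r)², which is positive for every r below 1. The loss remains under that reading.

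**Strata.** The gain from adding the four groups is not quantified, because the article gives no between-group variation for these scores.

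**The case against.** **The t test is valid.** This stands. With 1:1 randomization it does not inflate type I error, and ignoring the strata makes it conservative if anything. Chance baseline imbalance is already reflected in its standard error, so it is part of the same precision loss and not a second fault.

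**The size rests on assumed correlations.** This also stands. Five instruments over 6 and 12 months need not share one value. At r = 0.3 the gain is small: the detectable difference moves only from 0.295 to 0.282 SD.

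**The baseline surveys may not be a clean covariate.** The Visit Schedule and Assessments section lists consent, randomization, education and blood pressure measurement before "and baseline surveys". The list may not be chronological. If it is, the surveys come after an open allocation and after education, and the scores could already reflect knowledge of the arm. Adjustment is sound only if the surveys come first.

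**A stronger reading goes too far.** A reader might infer that these are completer analyses, biased whenever dropout relates to outcome, while the primary outcome is protected by imputation. The article does not support this. It names multiple imputation for the primary analysis and does not say how missing patient-reported scores are handled; a t test can be run on imputed data. Outcome-related dropout also need not bias the arm difference, for example when it shifts both arm means equally.

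Nor does the article show that the choice was made without a reason. It gives none, which is a different thing.

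**Conclusion.** The point holds as a matter of efficiency on secondary outcomes. The article fixes an unadjusted comparison for five scores and collects, but does not use, their baseline values. The avoidable variance is 9%, 25% or 49% of the t-test variance at assumed correlations of 0.3, 0.5 or 0.7, and using change scores would not recover all of it.

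The conclusion assumes a roughly linear relation between baseline and follow-up and surveys completed before the allocation is known. Type I error is not at issue. Bias from missing questionnaires is a possibility and has not been shown. The change is worth making because it needs no new data, but the trial's main result does not depend on it.

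**What to change.** 1. Make the main comparison of each score a linear model at each visit with arm, baseline score and the four randomization strata. Alternatively, use one repeated-measures model over both visits with the same terms plus visit and arm-by-visit. Either recovers the gain from baseline adjustment shown above.
2. Report the adjusted mean difference and 95% confidence interval at 6 and at 12 months. The unadjusted t test may stay as a supporting analysis, as the article already does for adverse events.
3. Confirm that participants complete the baseline surveys before they learn their allocation, and state this order. If they do not, reconsider the use of those scores as covariates.
4. State how missing patient-reported scores are handled. A repeated-measures model would also use participants seen at only one follow-up visit, under missing at random.

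The cost is analysis-plan wording and a check of the visit procedure. No extra visits, instruments or participants are needed.

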#### Additional Analyses

We plan a cost-effectiveness analysis that will follow the recommendations of Cost-Effectiveness in Health and Medicine, 2nd Panel [32] to present the analysis from both the societal and health care perspectives and to include an inventory of the non-health care impacts of the mGlide intervention. We will measure effectiveness by the differences in quality-adjusted life years (as derived from the EQ-5D-3L quality-of-life weights) across the 2 trial arms. Costs will represent the intervention cost and any differences in downstream health care and other costs for the societal perspective (productivity or time, informal care, travel) across the 2 arms. We will extrapolate quality-adjusted life years and cost differences using a 10-year stochastic event model. Thus, the cost-effectiveness analysis will meld both the trial follow-up experience of participants and their modeled experience for the remaining years, based on differences in HTN control rates between the 2 trial arms. Specifically, we will determine downstream health care utilization using a state transition (Markov) model using Monte Carlo microsimulation. Our team includes an experienced health economist (JN).

### Data Safety and Monitoring

We have convened a 5-member data safety monitoring board (DSMB) with expertise spanning the statistics of clinical trial monitoring, HTN, pharmacist-delivered care, vascular neurology, and cardiology. Following an initial meeting at study start, the DSMB meets approximately every 6 months.

## Results

Study enrollment commenced in March 2019. Through mid-March 2020, 101 participants were randomized with 52 to the mGlide arm and 49 to the state-of-clinical-care arm. In mid-March 2020, the University of Minnesota paused enrollments for non-COVID-19 research studies involving face-to-face participant contact. In response, the mGlide team developed protocols for remote enrollment including remote consent in REDCap and protocols to mirror the in-person enrollment process. We also developed a remote protocol for gathering the 6-month and 12-month follow-up data and BP measurements using Zoom. These have been approved by the IRB and the study sponsor and are currently in use. To date, we have enrolled 5 participants remotely and are completing the 6-month and 12-month follow-up visits. We will validate our remote BP measurement protocols against pre-COVID-19 in-person processes when our institution allows in-person research participant visits. The impact of COVID-19 is that the study timeline for completion of enrollment and intervention has been extended by 6 months; other possible effects on the study will be monitored.

To date, we have enrolled a total of 107 participants (54 intervention and 53 control participants). A total of 86 participants have completed their 6-month follow-up (primary BP endpoint), and 46 participants have completed their 12-month follow-up (secondary BP endpoint). Seven participants have withdrawn, and 1 participant has died. The study principal investigator reviews adverse events, and a team of 2 blinded study clinicians subsequently reviews these events. The study statisticians and DSMB review these and other study outcomes at the DSMB meetings.

## Discussion

HTN is a chronic disease requiring sustained efforts for long-term control. The mGlide RCT seeks to address the persistent and prevalent clinical challenge of poorly controlled HTN in a diverse sample of adults at elevated risk for stroke and CVD events. The study aims are to (1) evaluate clinical effectiveness of the mGlide intervention in comparison to usual clinical care; (2) improve clinical teams’ abilities to manage patients’ antihypertensive medications; (3) increase patient activation, patients’ satisfaction with care, and medication use self-efficacy and adherence as well as lower health care utilization; and 4) establish the cost-effectiveness of the mGlide intervention. Intervention participants monitor their BP daily with a wireless BP monitor and use their smartphone to transmit BP readings to a database automatically via an app. We then use the framework of glide paths to manage the transmitted BP data. The name of the intervention, mGlide, derives from the glide path concept of landing an airplane; an expected trajectory of BP readings is established for each patient with bounds set by guidelines and further adjusted by providers as needed. Although BP is monitored daily at home, the health care team accesses the BPs once a week and makes medication adjustments as needed, in collaboration with the patient’s PCP. We believe this approach will facilitate early intervention in an efficient manner while avoiding system information overload.

The key innovation of the mGlide trial is using a mobile technology platform to facilitate better HTN control through a collaborative patient-provider partnership in limited-resource health systems. Currently, 68% of US adults use smartphones (up from 35% in 2011) [33]. The mGlide system based on mobile technology uses the patient’s own smartphone. A free app allows the wireless monitor to interface with the smartphone. The app transmits the data to an online database. The database is free, and there is no patient service contract. Hence, mHealth is nimble and represents the next generation in technology. While small clinical trials have demonstrated the efficacy of mHealth in SMBP [11,15-17], we will demonstrate the feasibility of the mGlide in different clinical health systems including low-resource environments that might not be able to afford investment in telemonitoring services with an outside vendor.

Results from this study will provide evidence for the use of readily available mHealth technology for bridging the guideline-to-practice gap in HTN treatment for diverse patients in diverse health care systems. Importantly, our study is being implemented in low-resource health systems serving minority and low-income groups and thus will provide critical insights into enhancing HTN control in these elevated-risk patients who experience significant cardiovascular disparities.

## Appendix

Multimedia Appendix 1 Peer-review reports from the NIH.

## Abbreviations

AHA: American Heart Association
BP: blood pressure
CVD: cardiovascular disease
DSMB: data safety monitoring board
FQHC: federally qualified health centers
HTN: hypertension
IRB: institutional review board
mHealth: mobile health
PCP: primary care provider
PROBE: Prospective Randomized Open Blinded End-point
RCT: randomized controlled trial
SBP: systolic blood pressure
SMBP: self-measured blood pressure monitoring
